## Abstract

Naproxen is a widely used non-steroidal anti-inflammatory drug for the control of postoperative inflammatory signs and symptoms in dentistry. Its association with esomeprazole has been widely studied and has yielded good results for the control of acute pain, even with the delayed absorption of naproxen owing to the presence of esomeprazole. To further understand the absorption, distribution, and metabolism of this drug alone and in combination with esomeprazole, we will analyze the pharmacokinetic parameters of naproxen and its major metabolite, 6-O-desmethylnaproxen, in saliva samples. A rapid, sensitive, and selective liquid chromatography-tandem mass spectrometric method for the simultaneous determination of naproxen and 6-O-desmethylnaproxen in saliva will be developed and validated. Sequential saliva samples from six patients will be analyzed before and 0.25, 0.5, 0.75, 1, 1.5, 2, 3, 4, 5, 6 8, 11, 24, 48, 72, and 96 h after the ingestion of one naproxen tablet (500 mg) and esomeprazole-associated naproxen tablets (500 + 20 mg), at two different times. After liquid-liquid extraction with ethyl acetate and HCl, the samples will be analyzed using an 8040 Triple Quadrupole Mass Spectrometer (Shimadzu, Kyoto, Japan). Separation of naproxen and its major metabolic products will be performed using a Shim-Pack XR-ODS 75Lx2.0 column and C18 pre-column (Shimadzu, Kyoto, Japan) at 40°C using a mixture of methanol and 10 mM ammonium acetate (70:30, v/v) with an injection flow of 0.3 mL/min. The total analytical run time will be 5 min. The detection and quantification of naproxen and its metabolite will be validated, which elucidate the pharmacokinetics of this drug, thereby contributing to its proper prescription for the medical and dental interventions that cause acute pain.

## 1 Introduction

Naproxen is a non-steroidal anti-inflammatory drug of the propionic acid class widely used to manage chronic and acute pain, fever, swelling, and inflammation. Recently, a combination with esomeprazole has been introduced to the market to prevent gastrointestinal adverse reactions [1–3].

Naproxen ((S)-2-(6-methoxynaphthalen-2-yl)propanoic acid)is mainly metabolized by hydroxylation, forming 6-O-desmethylnaproxen, which then conjugates with glucuronic acid. Esomeprazole ((R)-5-Methoxy-2-(((4-methoxy-3,5-dimethylpyridin-2-yl)methyl)sulfinyl)-1H-benzo[d]imidazole) is the S-isomer of omeprazole, with gastric proton pump inhibitor activity. In the acidic compartment of parietal cells, esomeprazole is protonated and converted to the active achiral sulfonamide [4]. Several analytical methods have been developed to determine the concentrations of naproxen and 6-desmethylnaproxen using liquid chromatography–tandem mass spectrometry (LC-MS/MS) [5, 6], but none in saliva samples.

To study the pharmacokinetics (PK) of naproxen alone and in combination with esomeprazole in saliva samples and predict its functionality in cases of acute pain owing to delayed absorption, saliva samples will be collected several times after the administration of one pill of naproxen (500 mg) and naproxen combined with esomeprazole (500 mg + 20 mg), and concentrations of naproxen and its major metabolite 6-O-desmethylnaproxen will be determined. The use of saliva for PK tests makes collection simpler and more secure, without the need for a professional and with greater adherence to the study. Therefore, the aim of the present study was to disseminate the results of robust and reliable PK studies.

Additionally, the detection and quantification of naproxen and its metabolite will be validated to determine the PKs of this drug, thereby contributing to the development of a proper prescription for different medical and dental interventions that cause acute pain. The hypothesis of the present study is that the absorption of naproxen, when administered with esomeprazole, is slower than that when administered alone. Thus, the results of the study can be used to reassess the use of naproxen for pain control after medical and dental interventions that cause acute pain.

## 2 Material and methods

This project was approved by the Research Ethics Committee of the Bauru School of Dentistry/University of São Paulo (CAAE 49806115.0.0000.5417), registered in ClinicalTrials.gov (NCT03092193). All volunteers participating in this research will be fully informed about the project’s content and procedures and sign a consent form.

### 2.1 Chemicals and reagents

Naproxen, 6-O-desmethylnaproxen, esomeprazole, and piroxicam (internal standard, IS) were purchased from Sigma-Aldrich (São Paulo, Brazil). Methanol, ammonium acetate, and other chromatographic grade chemicals used in the tests were purchased from Merck (Hohenbrunn, Germany). During all experiments, water from a Milli-Q Plus purification system (Millipore, Belford, MA, USA) was used.

### 2.2 Preparation of standard solutions

Stock solutions of naproxen (1 mg/mL methanol), 6-O-desmethylnaproxen (1 mg/mL methanol), esomeprazole (500 μg/mL methanol), and IS (1 mg/mL methanol) were prepared. A dilution series from each stock solution (10 μg/mL)was used to construct standard curves. When not in use, solutions were stored in the dark at -20°C and all stages of the research were conducted under a sodium vapor lamp to avoid photodecomposition of naproxen, 6-O-desmethylnaproxen, esomeprazole, and the IS [7, 8].

### 2.3 LC-MS/MS

The concentrations of naproxen and its major metabolic, 6-O-desmethylnaproxen, were analyzed using an 8040 Triple Quadrupole Mass Spectrometer (Shimadzu, Kyoto, Japan)and piroxicam was used as an IS. Before performing the standard curve for naproxen, 6-O-desmethylnaproxen, esomeprazole, and the IS, the mobile phase was standardized to increase the reliability of the results that will be obtained from saliva samples in the PK studies [7]. As naproxen and esomeprazole ionize in different ways, only the PKs of naproxen and its major metabolite were investigated, as these are the drugs of most interest for pain control.

Initial analysis for drug characterization was performed by LC-MS/MS and separation was performed using a Shim-Pack XR-ODS 75Lx2.0 column and C18 pre-column (Shimadzu, Kyoto, Japan) at 40°C using a mixture of methanol and 10 mM ammonium acetate (70:30, v/v) with an injection flow of 0.3 mL/min. The total analytical run time was 5 min.

The chromatographic effluent was directed to the 8040 Triple Quadrupole Mass Spectrometer (Shimadzu, Kyoto, Japan). Mass spectrometry was performed following the information obtained in the optimization of ions in positive/negative ionization mode using ionizing electrospray, with monitored selection for quantitative analysis. The voltage of the ionization electrospray capillary was 4.5 kV. Source and desolvation temperatures were maintained at 250°C and 350°C, respectively. Nitrogen was used as the mist gas at 3.0 L/min and argon gas as the collision gas at approximately 230 kPa. The cone voltage was defined for each transition and drug molecular ions were fragmented by the variable collision energy. All conditions were achieved by the direct injection of standard drug solutions of naproxen and 6-O-desmethylnaproxen without the separation column, resulting in transitions in which specific father/son ions were employed. The time of analysis for each event was 0.075 ms. The measurements were performed in multiple reaction monitoring mode to quantify the transitions presented in Fig 1. The peak areas for all components were integrated automatically using the LabSolutions software, version 5.97(Shimadzu, Kioto, Japan). The transitions considered for the quantification and qualification of the peaks are shown in Table 1.

**Fig 1 pone.0236297.g001:**
[figure not shown]
Multiple reaction monitoring mode to quantify the naproxen, 6-O-desmethylnaproxen, and piroxicam transitions.

**Table 1 pone.0236297.t001:** Quantifier and qualifier product ions used in the analysis.

**O-Desmethylnaproxen**				
**Type**	**m/z**	**Inten**	**Act %**	**Idenf. Rang %**
T	214.900>171.250^a^	199246	100.00	100%
Ref 1	214.900>169.250^b^	49605	24.90	-
Ref 2	214.900>143.050	3283	1.65	-
**Naproxen**				
**Type**	**m/z**	**Inten**	**Act %**	**Idenf. Rang %**
T	228.900>170.30^a^	513749	100.00	100%
Ref 1	228.900>169.250^b^	336855	65.57	-
Ref 2	228.900>185.200^b^	288128	56.08	-
**Piroxicam**				
**Type**	**m/z**	**Inten**	**Act %**	**Idenf. Rang %**
T	331.900>95.100^a^	33688	100.00	100%
Ref 1	331.900>121.050	15274	45.37	-
Ref 2	331.900>78.100^b^	23870	70.90	-

^a^Quantifier: the most intense peak.

^b^Qualifier: a second peak (SRM)t has been used as a qualifier for the same analysis.

### 2.4 Sample preparations

Drug-free saliva blanks (400 μL) were enriched with 5 ng of IS + 6.25 ng of naproxen and 6-O-desmethylnaproxen and 400 μL of 0.5 M HCl for the first calibration standard point. For the standard calibration curve, eight serial dilutions were performed and the final mass was equal to 0.024 ng of naproxen and 6-O-desmethylnaproxen. The IS mass was the same for all curve points. These standard calibration curve points were extracted with 2 mL of ethyl acetate in 15 mL polypropylene tubes, shaken vigorously for 15 min at high speed (Heidolph Multi Reax EU, Heidolph Instruments GmbH & Co., KG, Schawaback, Germany) and centrifuged at 2,500 g at 4°C for 10 min. The organic phase (~1.8 mL) was then transferred and evaporated under airflow at room temperature in the chamber.

Saliva samples before naproxen alone and naproxen with esomeprazole intake (t = 0) were analyzed to ensure that there was no interference. After evaporation, the residues were dissolved in 100 μL methanol:10 mM ammonium acetate (70:30, v/v, isocratic), vortexed for 1 min, transferred to inserts, and then 5 μL of this solution was used for high-performance liquid chromatography.

### 2.5 Volunteer sample preparation

The PK study of naproxen and its major metabolite, 6-O-desmethylnaproxen, will be performed in six healthy volunteers, who will have sequential collections of saliva before and 0.25, 0.5, 0.75, 1, 1.5, 2, 3, 4, 5, 6 8, 11, 24, 48, 72, and 96 h after the ingestion of a naproxen tablet (500 mg) and esomeprazole-associated naproxen tablets (500 + 20 mg), at two different times, separated by 1–2 months. Samples will be centrifuged for 10 min (2,500 rpm) and the supernatant stored at -20°C until analysis.

The quantified PK parameters of naproxen and its major metabolite, 6-O-desmethylnaproxen, in saliva, alone and in combination with esomeprazole, will be estimated using the mean area under the curve, 0–72 h (AUC_0-72_)and AUC_infinity_, predicted total clearance (Clt/F), volume of distribution (Vd/F), and elimination half-life (t_1/2_) based on concentrations obtained experimentally using a non-compartmental model with first-order elimination. These PK analyses will be performed using Phoenix WinNonlin® 8.1 software (Pharsight Corp., Mountain View, CA, USA). The data will be presented as mean ± standard deviation.

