### 2.6 PK from six volunteers

In addition to validating the method for the detection and quantification of naproxen and its metabolite, 6-O-desmethylnaproxen, the PKs of six volunteers who will take one pill of naproxen (500 mg) and naproxen associated with esomeprazole (500 mg + 20 mg) will be investigated.

This study was registered as a clinical trial at ClinialTrials.gov (NCT030902193) after the analysis carried out by the website, as when prescribing these two drugs (naproxen alone and naproxen in combination with esomeprazole), a series of side effects may occur in a small portion of the population, such as allergies, gastric irritation, intestinal irritation, gastritis, colitis, and gastrointestinal bleeding. Such reports will be noted and analyzed during the clinical trial.

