### 2.8 Statistical analysis

After analyzing the PK and pharmacodynamic results using the Phoenix WinNonlin software (version 8.1), the data will be organized descriptively and a paired *t-*test will be performed to compare naproxen absorption after volunteers are administered, at two different times, naproxen alone or naproxen in combination with esomeprazole.

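### The order of the two products is not stated and the paired t-test has no period term, so the plan permits treatment and period to be confounded

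*Protocol article*

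**What the plan says.** Section 2.5 says that the pharmacokinetic study "will be performed in six healthy volunteers, who will have sequential collections of saliva" after each of the two products, taken "at two different times, separated by 1–2 months". Section 2.6 confirms that the same six people take both.

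Section 2.8 names one inferential analysis, a paired t-test that "will be performed to compare naproxen absorption after volunteers are administered, at two different times, naproxen alone or naproxen in combination with esomeprazole". The hypothesis resting on it is in the Introduction: "the absorption of naproxen, when administered with esomeprazole, is slower than that when administered alone".

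No section mentions randomisation, sequence, counterbalancing or a period effect. No section says that every volunteer takes the products in the same order. Naproxen alone is named first in the Abstract, the Introduction and Sections 2.4, 2.5, 2.6 and 2.8, but none of these assigns an order.

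**The concern.** In a two-period comparison, only the order of administration can separate the effect of the product from the effect of the occasion. If everyone takes the products in one order, each paired difference is the treatment effect plus whatever changed between the two visits, and no later analysis can split them.

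The article itself gives reasons why occasions might differ. They are one to two months apart, and samples are frozen until analysis (2.5). If all samples are assayed together, those from the first occasion are older; if not, the assay batches differ. The stability tests in 2.7 cover short-term storage, post-processing and freeze–thaw cycles, and accept results within 15% of nominal. The gap between visits guards against carry-over, not against these differences.

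The trial's only between-product comparison is at stake. The order must be set before the first dose, so an analysis plan written later cannot restore it.

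**Working it through.** The article gives no alpha, standard deviation, effect size or power, so there is no figure of its own to reproduce.

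**Inputs from the article:** n = 6, two products per volunteer, two occasions, plain paired t-test (2.5, 2.6, 2.8).

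**Assumptions:** two-sided alpha 0.05, no carry-over, no true treatment effect, within-subject CV 25%, period shifts of 0.1, 0.2 and 0.3 on the log scale. For scale, the 15% stability limit in 2.7 corresponds to ln(1.15) = 0.14 or |ln(0.85)| = 0.16. That is a tolerance, not an expected drift.

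**1. Can treatment and period be separated?** A model with six volunteer effects, one period effect and one treatment effect has 8 parameters. With one fixed order the design matrix has rank 7, so they cannot be separated. Adding volunteers in the same order does not help. With a 3:3 split the rank is 8 of 8.

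**2. Bias by split.** Let τ be the treatment effect (combination minus alone) and π the period effect (second minus first occasion). A volunteer taking naproxen alone first contributes τ + π on average; one taking it second contributes τ − π. With k volunteers taking it first, the mean paired difference is τ + π(k − (6 − k))/6.

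| Split | Share of π in the estimate |
|---|---|
| 3:3 | 0 |
| 4:2 | 1/3 |
| 5:1 | 2/3 |
| 6:0 | 1 |

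Independent coin tosses give an exact 3:3 split with probability 20/64 = 31%, so balance has to be built in.

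**3. False-positive rate under one fixed order.** Log-scale within-subject SD = √ln(1 + 0.25²) = 0.246. SD of the paired difference = √2 × 0.246 = 0.348. The paired t statistic is noncentral t with 5 df and noncentrality π√6/0.348, compared with 2.571.

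| Period shift (log scale) | Noncentrality | Rejection rate |
|---|---|---|
| 0.1 | 0.70 | 8.9% |
| 0.2 | 1.41 | 21.0% |
| 0.3 | 2.11 | 40.1% |

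Without the CV assumption, a period effect of 0.25, 0.5 or 1 SD of the difference gives 8.0%, 17.1% or 50.7%.

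**4. Balanced or nearly balanced orders, same assumptions, by simulation** (shifts 0.1 / 0.2 / 0.3).

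| Split and test | Rejection rate |
|---|---|
| 3:3, plain paired t-test | about 4.3% / 2.7% / 1.3% |
| 3:3, period-adjusted test (4 df) | about 5% throughout |
| 4:2, plain paired t-test | about 4.7% / 4.0% / 3.0% |

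At 3:3 the plain test is unbiased but conservative, because the period effect inflates the spread of the differences. At 4:2 the estimate is biased but the test is not inflated.

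**5. Price of the adjusted analysis.** Its standard error is (σ_d/2)√(1/k + 1/(6 − k)), where σ_d is the SD of the paired difference. At 3:3 this is 0.408σ_d, the same as σ_d/√6 for the plain paired test. The cost is one degree of freedom: the critical value rises from 2.571 to 2.776, a ratio of 1.080. Allowing for the expected sample SD with 4 and 5 df, expected interval width rises by 1.080 × 0.9400/0.9515 = 1.067, about 7%.

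**The case against.** The strongest reply is that silence is not a design fact. A journal article condenses a fuller protocol, and an allocation list may exist there. Naming naproxen alone first is ordinary reference-then-test wording. This stands: a reader might infer from it that all six take naproxen alone first, and the article does not support that.

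The false-positive figures need that lopsided case. At 3:3 or 4:2 the plain paired t-test rejects at or below 5%. This also stands, so the 9%, 21% and 40% are conditional on a 6:0 order and on an assumed CV and shift.

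A reader might also infer that any drift between visits would pass for an esomeprazole effect, or that six volunteers are too few to repair it. Neither holds. A purely proportional assay drift would change AUC, Clt/F and Vd/F but not the time of the peak, which bears on a hypothesis about slower absorption. The internal standard and the inter-assay checks limit some assay drift. Irrecoverability comes from a single order, not from n = 6: if both orders occurred, period can still be adjusted for from the dosing dates.

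The reply that all this belongs in an analysis plan does not stand. A period term could be added there, but the order is fixed by conduct before dosing, and the article reports the spacing and the test without it.

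**Conclusion.** The point holds in a limited form. As written, the plan permits a single order, under which treatment and period are fully confounded whatever the sample size, and it permits unbalanced splits that carry one third (4:2) or two thirds (5:1) of the period effect into the estimate. These fractions follow from the design alone.

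The inflation of the test to about 9%, 21% or 40% is illustrative, because the article gives neither a within-subject CV nor a period effect. If the order is in fact balanced 3:3, the named test is unbiased and errs only towards caution. The change should be made because this is the trial's only between-product comparison and the remedy is cheap.

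**What to change.** In 2.5, state that the six volunteers are randomised 3:3 to the two orders (alone then combination, or the reverse), using a balanced list rather than separate coin tosses. In 2.8, replace the plain paired t-test by the period-adjusted crossover analysis, which compares within-volunteer differences between the two sequences on 4 df.

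The cost is a list for six people, a sentence in each section and one error degree of freedom.

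If dosing has already been done, report the order each volunteer followed. If both orders occurred, adjust for period. By the formula in step 5 the standard error is then 0.408, 0.433 or 0.548 times the SD of the paired difference at 3:3, 4:2 or 5:1. If only one order occurred, state period confounding as a limit on the conclusion.

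### Clt/F and Vd/F are planned for a metabolite that is never dosed, and for naproxen the saliva-based values carry names that belong to systemic quantities

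*Protocol article*

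**What the plan says.** Section 2.5 of the protocol article gives a single parameter list for two analytes in one matrix: "The quantified PK parameters of naproxen and its major metabolite, 6-O-desmethylnaproxen, in saliva, alone and in combination with esomeprazole, will be estimated". Besides two AUCs, the list contains "predicted total clearance (Clt/F), volume of distribution (Vd/F), and elimination half-life (t_1/2_) based on concentrations obtained experimentally", obtained "using a non-compartmental model with first-order elimination". Nothing limits Clt/F or Vd/F to naproxen.

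Three other statements bear on this:

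- **Dose.** The same section describes "ingestion of a naproxen tablet (500 mg) and esomeprazole-associated naproxen tablets (500 + 20 mg"). No metabolite is administered.
- **Origin of the metabolite.** The Introduction says that naproxen "is mainly metabolized by hydroxylation, forming 6-O-desmethylnaproxen, which then conjugates with glucuronic acid". No fraction converted is stated.
- **Matrix.** Section 2.5 describes saliva collection only. The article describes no plasma sampling in the volunteers and gives no saliva/plasma ratio.

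Section 2.8 plans a paired t-test on naproxen absorption. It does not name Clt/F or Vd/F as the tested quantity.

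**The concern.** In a non-compartmental analysis after an oral dose, clearance over F is dose divided by AUC to infinity, and volume over F divides that again by the terminal slope. Both need the amount of that analyte entering the body. For 6-O-desmethylnaproxen this amount is an unknown share of the naproxen dose. The plan therefore lists two metabolite parameters that its design cannot deliver.

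For naproxen the dose is known, but the concentrations come from saliva. Total clearance and volume of distribution describe the whole body and are defined against plasma or blood concentration. Dose over saliva AUC has the same units but is a different quantity unless saliva and plasma concentrations are equal.

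At stake is the correctness of a set of published descriptive values. The abstract sets out to describe distribution and metabolism as well as absorption. Vd/F is the listed parameter that speaks to distribution, and the metabolite values are the result on metabolism.

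**Working it through.** The plan states no PK value to reproduce, so the check compares what the formulas return with what they are called.

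**Inputs from the article**

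- Dose: 500 mg naproxen in both periods; no metabolite dose (section 2.5).
- Matrix: saliva only (section 2.5).
- Metabolite/parent mass ratio: from the precursor ions in Table 1 ("214.900>171.250" for the metabolite; 228.900 for naproxen). 214.9/228.9 = 0.94.

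**Inputs not in the article, assumed**

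- fm, the fraction of naproxen converted to the metabolite: 0.3 to 0.8.
- R, the saliva/plasma ratio: 0.01 to 1.

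**Step 1: naproxen.** With saliva AUC = R × plasma AUC,

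Dose / AUC(saliva) = (Clt/F) / R.

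The factor by which the reported value differs from Clt/F is 1/R:

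| R (assumed) | Factor |
|---|---|
| 0.01 | 100 |
| 0.1 | 10 |
| 0.5 | 2 |
| 1 | 1 |

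Vd/F is this quantity divided by the terminal slope. A constant R leaves the slope unchanged, so Vd/F carries the same factor. If R were above 1, the value would be too small (factor 0.5 at R = 2), so the documents do not fix even the direction.

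**Step 2: metabolite.** The only dose available is that of naproxen. The mass of metabolite formed is F × fm × 0.94 × Dose, so

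Dose / AUC(metabolite, saliva) = CLm / (F × fm × 0.94 × R),

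with R here the metabolite's own ratio. Against CLm/F the factor is 1/(fm × 0.94 × R). At R = 1:

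- fm = 0.8: 1/(0.8 × 0.94) = 1.3
- fm = 0.3: 1/(0.3 × 0.94) = 3.5

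At R below 1 these grow by 1/R. For example, fm = 0.3 with R = 0.1 gives about 35.

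**Step 3: numerical check of the metabolite identity.** A parent-to-metabolite model was integrated with arbitrary values: Dose 500 mg, F = 1, R = 1, fm = 0.3, parent CL 0.5 L/h and V 8 L, metabolite CLm 5 L/h and Vm 15 L.

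- Metabolite AUC = 0.3 × 0.939 × 500 / 5 = 28.17 mg·h/L.
- Dose over that AUC = 500 / 28.17 = 17.7 L/h, against a true 5 L/h.
- Metabolite terminal slope = 0.0625/h. This is the parent's rate (0.5/8), not the metabolite's (5/15 = 0.333/h).
- The resulting volume = 17.7 / 0.0625 = 284 L, against a true 15 L.

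In this example the volume fails twice: through the missing fm, and because the slope belongs to the parent. For the same reason a metabolite half-life from the terminal slope may describe the elimination of naproxen.

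**The case against.** The strongest defence has four parts.

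- **The article is condensed.** One sentence compresses both analytes and all parameters. A fuller plan may say which outputs apply to which analyte, and the article never says outright that 500 mg will be divided by metabolite AUC. This softens the point but does not remove it. The sentence as published assigns the list to both analytes, and no other dose exists to enter.
- **The matrix is disclosed.** The sentence says the parameters are in saliva, and the whole article is about saliva. This stands, and it reduces the naproxen part to labelling. But F denotes bioavailability and does not absorb a saliva/plasma ratio, and the word total still claims a systemic quantity.
- **The magnitudes rest on assumptions.** This stands in full. A reader might infer that naproxen values will be 10 to 100 times too large. That follows only from assuming R between 0.01 and 0.1, and no figure in the article supports it.
- **The trial's question does not depend on these parameters.** This also stands. The hypothesis concerns slower absorption. A reader might infer that Clt/F will be tested between treatments, but section 2.8 names only naproxen absorption, and section 2.5 presents the parameters descriptively. A reader might also infer harm to prescribing. The article ties its prescribing aim to acute pain and delayed absorption, and nowhere says that saliva clearance or volume will guide it.

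**Conclusion.** The point holds, within limits. For 6-O-desmethylnaproxen it is a matter of definition and needs no assumed value: without a metabolite dose or a known fm, the listed clearance and volume cannot be estimated. For naproxen it is a misnomer: dose over saliva AUC equals Clt/F only if R is 1, which the trial neither states nor measures, and the same applies to Vd/F.

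The documents do not allow the size to be computed. The 1.3- to 3.5-fold (metabolite) and 1- to 100-fold (naproxen) ranges are illustrations that rest wholly on the assumed fm and R.

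The effect is confined to the reported descriptive parameters. Saliva AUC remains a valid descriptive measure. The paired comparison of naproxen absorption does not use Clt/F or Vd/F, and constant factors cancel in a within-subject ratio if R and fm are the same in both periods.

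**What to change.** In section 2.5, split the parameter list by analyte.

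- **6-O-desmethylnaproxen:** delete Clt/F and Vd/F. Report saliva AUC, apparent terminal half-life with a note that it may reflect the elimination of naproxen, and the molar metabolite-to-parent AUC ratio (mass ratio of AUCs divided by 0.94), described as a saliva ratio.
- **Naproxen:** either drop Clt/F and Vd/F, or keep them labelled as apparent saliva values (for clearance, dose/AUC in saliva) and state that they are not systemic clearance or volume.

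The cost is a few words, two fewer metabolite parameters, and one ratio computed from concentrations already planned. No new samples, visits or assays are needed, and section 2.8 does not change.

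### The hypothesis is slower absorption, but no listed PK parameter measures absorption rate and the variable for the paired t-test is not named

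*Protocol article*

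**What the plan says.** - **Hypothesis (Introduction).** "The hypothesis of the present study is that the absorption of naproxen, when administered with esomeprazole, is slower than that when administered alone". The same section says the study should "predict its functionality in cases of acute pain owing to delayed absorption".
- **Parameters (2.5).** The list is "mean area under the curve, 0–72 h (AUC_0-72_)and AUC_infinity", then "predicted total clearance (Clt/F), volume of distribution (Vd/F), and elimination half-life", estimated "using a non-compartmental model with first-order elimination". Nothing in the wording marks the list as examples only.
- **Test (2.8).** A paired t-test "will be performed to compare naproxen absorption after volunteers are administered, at two different times", the two products. The variable to be tested is not stated.
- **Sampling (2.5).** There are 16 post-dose times from 0.25 to 96 h, of which 10 fall at or before 6 h, in six volunteers who each receive both products.

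Tmax, Cmax, lag time, an absorption rate constant, mean absorption time and early partial AUC appear nowhere in the article.

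**The concern.** "Slower" is a statement about rate. AUC describes how much drug is absorbed, and clearance, volume and half-life describe what happens to it afterwards. A comparison built on the listed parameters would look at quantities that should be nearly equal even if the hypothesis is true. A result of no difference could then be read as no delay. The Introduction intends the results to inform the use of naproxen in acute pain, where the delay is the point of interest.

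The other route is also unsatisfactory. If the investigators test something outside the list, such as Tmax, the choice among several possible measures is open until the data are in hand, with only six volunteers.

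**Working it through.** The article gives no effect size, variability, alpha or power for this comparison, so there is no figure of its own to reproduce.

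**Step 1: what the listed parameters depend on.** With bioavailability F, elimination constant λz and absorption constant ka:
- AUCinf = F·Dose/CL
- Clt/F = Dose/AUCinf
- Vd/F = Dose/(AUCinf·λz)
- t1/2 = ln 2/λz

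None contains ka or lag time, provided ka exceeds λz and F is the same for both products. AUC0-72 is truncated, so it depends on them slightly.

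**Step 2: size of the effect.** I used a one-compartment curve, C(t) proportional to ka/(ka−ke)·[exp(−ke·u) − exp(−ka·u)], with u = t − lag and ke = ln 2/t1/2. Then Tmax = lag + ln(ka/ke)/(ka−ke). The assumed values, none of them from the article, are t1/2 of 10, 15 and 20 h, with ka = 2/h and no lag against ka = 0.5/h and a 2 h lag.

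| t1/2 | ke (/h) | Tmax, fast | Tmax, delayed | AUC0-72 ratio | AUC0-4 ratio |
|---|---|---|---|---|---|
| 10 h | 0.0693 | 1.74 h | 6.59 h | 0.998 | 0.23 |
| 15 h | 0.0462 | 1.93 h | 7.25 h | 0.993 | 0.22 |
| 20 h | 0.0347 | 2.06 h | 7.74 h | 0.988 | 0.22 |

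For example, at 10 h: ln(2/0.0693)/(2 − 0.0693) = 1.74 h, and 2 + ln(0.5/0.0693)/(0.5 − 0.0693) = 6.59 h. The ratios for AUCinf, Clt/F, Vd/F and t1/2 are 1.00. A pure 2 h lag shifts Tmax by exactly 2 h and lowers AUC0-72 by 0.1% to 0.7%.

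**Step 3: the protocol's own sampling times.** Non-compartmental estimates were computed on the scheduled grid, with reference ka 1.5/h, t1/2 of 8, 14 or 24 h, and lags of 1 to 3 h and/or ka cut to one half or one third. AUC0-72 changed by −0.1% to −2.4%. AUCinf, Clt/F and Vd/F changed by at most about 1.1%, and t1/2 by 0.0%. Tmax moved from 2–3 h to 3–8 h, and AUC0-4 fell by 17% to 94%.

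**Step 4: rejection rates.** These are for a two-sided 5% paired t-test on untransformed differences, n = 6, t1/2 14 h, with 1,000 simulated trials per setting. Assumed within-subject variability is 15% and assay noise 10%, except in the last row, where both are 5%.

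| Scenario | Listed parameters | Tmax | AUC0-4 | Cmax |
|---|---|---|---|---|
| No delay | 0.04–0.05 | 0.04 | 0.04 | 0.04 |
| 2 h lag | 0.04–0.05 | 0.68 | 1.00 | 0.05 |
| 3 h lag, ka 0.5/h | 0.05–0.06 | 1.00 | 1.00 | 0.33 |
| 2 h lag, 5% variability | 0.04–0.06 | 0.92 | 1.00 | 0.06 |

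On the listed parameters the test stays near its false-positive rate even for a large delay. On a rate measure, the same six volunteers and the same samples can show it.

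**The case against.** A reader might infer that the planned test cannot detect a delay and that the hypothesis is left untested. The article does not support that. Section 2.8 does not apply the t-test to the list in 2.5; it speaks only of naproxen absorption. Near-zero sensitivity follows only if the listed parameters are what is tested. This objection stands, and the point is worded accordingly.

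It can also be said that a condensed article may leave the exact test variable to a fuller document. That weakens any complaint about 2.8 taken alone. It does not answer 2.5, where the article prints a list that leaves out the quantity its hypothesis is about.

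The invariance is conditional too. A difference in bioavailability would move AUC, Clt/F and Vd/F, and absorption slower than elimination would change the apparent half-life. A change in AUC caused by bioavailability would still be a change in extent, so it would not establish slower absorption.

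Finally, adding Tmax and keeping the t-test would be a poor remedy. Tmax can take only scheduled times, and beyond 6 h these are 8, 11 and then 24 h, which is coarse for a delayed peak at 6.6 to 7.7 h. This stands and shapes the fix.

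**Conclusion.** The mismatch is real and internal to the article: a rate hypothesis, a parameter list confined to extent and disposition, and a test with no named variable. Either the test uses the listed parameters and has almost no ability to detect a delay, or it uses a measure that has not been pre-specified. Both readings call for the same correction.

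The size rests on assumed ka, lag, half-life and variability, on equal average bioavailability, and on first-order absorption faster than elimination. Across the ranges tried, the listed parameters move by at most 2.4%. The qualitative conclusion follows from the formulas in Step 1 and does not depend on the particular values. It should be corrected before analysis because it concerns the study's only stated hypothesis.

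**What to change.** 1. **In 2.5**, add absorption-rate measures for naproxen: an early partial AUC (for example 0–4 h), Tmax and lag time. Cmax can be reported as weak support only, since a pure lag leaves it unchanged.
2. **In 2.8**, name one rate measure as the variable for the primary paired comparison, with a test suited to it. One option is a paired t-test on the log of early partial AUC. If Tmax is chosen, use a paired non-parametric test. Under the assumptions above early partial AUC was the more sensitive. Its window should be fixed in advance, with a rule for a value of zero, which has no logarithm and would arise if the lag outlasted the window.
3. **Label** AUC0-72, AUCinf, Clt/F, Vd/F and t1/2 as extent and disposition descriptors that do not test the hypothesis.

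The cost is a change of wording and slightly more analysis. No new samples are needed: 8 of the 16 post-dose times fall at or before 4 h and 10 at or before 6 h. The remaining limitation is a coarse Tmax if the delayed peak falls after 6 h.
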